### Statistical analysis

5.8

A trained statistician from CRC will complete all the statistical analysis, by Statistical Packages of Social Sciences software (version 24.0). Intention-to-treat approach for effectiveness and safety analysis will be used. As dealing the missing values, last-observation-carried-forward method will be applied. The mean ± standard deviation will be chosen for the description of continuous variables and the percentage is chosen to describe the variable values. Continuous variables, which are kept in the normal distribution, will be analyzed by Student *t* test; or else, nonparametric tests will be adopted. All statistical tests are 2-sided and *P* < 0.05 means statistically significant.

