### Randomization and allocation

4.4

Shanghai Medical Clinical Research Center (CRC, website: http://www.scrcnet.org) will control the randomization and create a random number listing by SAS 9.1 PROC PLAN. This list contains 2 matching groups: 1st group is sequence number of inclusion, 2nd is the THJG or placebo group.

Pharmaceutical factory will call the CRC to acquire the random number listing after completing drugs, then attach the sequence number to boxes of medicine (THJG or placebo) according to the listing. Medicine will be transported to the CRC, administrated by a trained staff.

All the investigators (except for the CRC and pharmaceutical factory) will not know the corresponding relations between sequence numbers and different groups until the trials are completed.

When a participant is eligible to be included, the investigator will make a central telephone call and give him/her the medicine (THJG or the placebo) from the CRC administrator according to the central call.

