### Sample size calculation

5.7

We conducted a pre-experiment of THJG and placebo treating SCAD from June 2018 to December 2018. According to the formula, 

, N1 and N2 are the patient numbers in THJG group and placebo group; *Z*_1–*α*_ = 1.96 when *α* = 0.05; *Z*_1–*β*_ = 1.282 when 1 − *β* = 0.90; *σ* (standard deviation of 2 groups) = 7.7; *k* = 1; *μ*_*r*_–*μ*_*c*_ (the difference of integral TCM syndrome score of THJG and control group) = 4; Δ = 0. Therefore, we plan to recruit 80 participants in total (40 of them in each group) to achieve a 90% power and a 2-sided 5% significance level in detecting the therapeutic differences between 2 groups.

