## Discussion

6

The treatment of SCAD has been significantly improved in recent years, especially the inflammation theory gains more attention. But to benefit patients and ameliorate the inflammation condition as many, these treatments wait to be updated. THJG consists of *R corydalis*, *S persicae*, *F carthami*, *R chuanxiong*, *R paeoniae rubra*, *R salviae miltiorrhizae*, *R angelicae sinensis*, *R rehmanniae*, *Fructus aurantii immaturus*, *R cyperi*, and *Olibanum*. Previous study proved that the main components *S persicae* and *F carthami* could alleviate inflammation and regular apoptosis, suggesting the potential beneficial effect of THJG on SCAD that should be valued by critical-designed trial.

We went through PubMed, Web of Science, Embase, the Cochrane Library, China National Knowledge Infrastructure, Wan Fang Database, VIP Journal Integration Platform, Chinese BioMedical database, and Clinical Trials up to March 2019, noticing no evidence about the efficiency and safety of THJG in treating SCAD patients. Therefore, this clinical trial will be the 1st multicenter, randomized, double-blind, placebo-controlled research that investigates the efficacy, safety, and inflammation improvement of THJG in treating SCAD.

To assure the exploration reliability, we design a 3-center, randomized, double-blind, controlled clinical trial. In addition, TCM syndrome score, a widely used for evaluation of Chinese herbs treatment, will be used to measure the symptoms improvement of the SCAD patients. Inflammation indexs, SAQ, and MACE also will be observed. Furthermore, we will evaluate the patients’ quality of life using AIS and SF-36. The safety of THJG will be evaluated according to patients’ feelings and laboratory tests, such as blood routine, feces and urine routine, kidney and liver function, BNP, echocardiography, and electrocardiograph.

The outcomes of this research will answer whether THJG is an effective drug to treat SCAD, especially to improve the inflammation condition. Its positive results will offer SCAD patients and physicians a different treatment option. Furthermore, the trial can provide proof of THJG about life quality changing, drug safety, and symptom severity relieving.

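### Section 5.8 fixes intention-to-treat for safety as well as efficacy; adverse events and laboratory safety should mainly be analysed in dosed patients by product received (minor)

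*Protocol article*

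**What the plan says.** Section 5.8 (Statistical analysis) of the protocol article sets the analysis population in one sentence: "Intention-to-treat approach for effectiveness and safety analysis will be used". The sections on interventions, randomisation, blinding, safety assessments and data collection say how product is supplied and how adverse events are recorded. None of them defines a safety set, requires at least one dose, or groups patients by the product they received.

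Section 4.4 describes supply. The factory obtains the random list and will "then attach the sequence number to boxes of medicine (THJG or placebo) according to the listing". A box is then released for each eligible patient after a central telephone call. Section 4.1 has dosing begin at Visit 1, and patients prepare and take the granules themselves. Section 5.3 lets patients withdraw at any time and has adverse effects asked about at each visit. Section 5.2.4 counts MACE from randomisation.

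On size, section 5.7 says "we plan to recruit 80 participants in total (40 of them in each group". On purpose, the Discussion says that "the trial can provide proof of THJG about life quality changing, drug safety, and symptom severity relieving".

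**The concern.** Intention-to-treat answers a question about assignment. For efficacy, the dilution it brings generally works against the claim being made. For harm it can work in favour of the claim, because a smaller observed excess on THJG reads as reassurance.

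Two kinds of patient are affected. One who is randomised but takes nothing remains in the adverse-event denominator of the assigned arm. One who is handed the other product by mistake has any resulting events counted against a product not taken.

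At stake is how the safety result reads in a trial with about 40 patients on THJG. The Discussion reports finding no earlier evidence on the product's safety in this disease, so these data would carry some weight.

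This is a rule the article states, not a detail left to a later document. A statistical analysis plan with a dosed, as-received safety set would have to depart from section 5.8.

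**Working it through.** **Plan's own figures.** The article gives no adverse-event rate, no never-dosed rate and no box-error rate, so there is no safety figure to reproduce. Its only computable figure is the sample size. With SD 7.7, difference 4, 90% power and two-sided 5%, 2 × (7.7 × (1.96 + 1.282) / 4)² = 77.9, or 78 per arm rather than 40. That is a separate matter. Here 40 per arm serves only as the denominator.

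**Inputs.** From section 5.7: 40 per arm. Assumed, for illustration only: event rates pT = 20% on THJG and pP = 10% on placebo; never-dosed shares qT and qP of 1, 2 or 4 in 40; a wrong-product share m of 1 or 2 in 40 in each arm; an event rate u in undosed patients of 0% or 10%.

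**Formula.** Expected intention-to-treat rate in an arm = (1 − q) × [(1 − m) × own rate + m × other arm's rate] + q × u.

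**Wrong product only.** The difference becomes (1 − 2m)(pT − pP), so it always moves towards zero in expectation.
- m = 1/40: 10 × 0.95 = 9.5 points.
- m = 2/40: 10 × 0.90 = 9.0 points.
- With a wider assumed contrast of 25% versus 5%, k swapped pairs give 20 × (40 − 2k)/40 = 19, 18 and 17 points for k = 1, 2, 3.

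**Never dosed, effect on one arm.** The THJG rate is 20% × (40 − n)/40 if the n undosed patients have no events.
- n = 1, 2, 4: 19.5%, 19.0%, 18.0%.
- If the undosed have events at u = 10%: 19.75%, 19.5%, 19.0%.

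**Never dosed, effect on the contrast.** The difference is (pT − pP) − qT(pT − u) + qP(pP − u). With equal shares q it is (1 − q)(pT − pP), whatever u is.

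| Never dosed (of 40) | u | THJG | Placebo | Difference (points) | Risk ratio |
|---|---|---|---|---|---|
| none | – | 20.0% | 10.0% | 10.0 | 2.00 |
| 1 in each arm | 0% | 19.5% | 9.75% | 9.75 | 2.00 |
| 4 in each arm | 0% | 18.0% | 9.0% | 9.0 | 2.00 |
| 4 in each arm | 10% | 19.0% | 10.0% | 9.0 | 1.90 |
| 4 on THJG only | 0% | 18.0% | 10.0% | 8.0 | 1.80 |
| 4 on placebo only | 0% | 20.0% | 9.0% | 11.0 | 2.22 |
| 4 on placebo only | 10% | 20.0% | 10.0% | 10.0 | 2.00 |

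**Both together, balanced.** The factor is (1 − q)(1 − 2m). One of each per arm gives 0.975 × 0.95 = 0.926, or 9.26 points. Two of each gives 0.95 × 0.90 = 0.855, or 8.55 points. Four never dosed and two wrong boxes give 0.90 × 0.90 = 0.81, or 8.1 points.

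**Zero events.** If no event of a given type is seen on THJG, the exact one-sided 95% upper bound is 1 − 0.05^(1/n): 7.2% for n = 40 and 8.0% for n = 36. With 4 of 40 never dosed, intention-to-treat reports the first, while the exposed patients support only the second.

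**Scale.** The standard error of a 20% rate in 40 patients is √(0.20 × 0.80 / 40) = 6.3 points. That of 25% versus 5% is √(0.25 × 0.75/40 + 0.05 × 0.95/40) = 7.7 points. Every shift above is well inside sampling error.

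**The case against.** The strongest case against runs as follows. Comparing harms by randomised group is legitimate, since it keeps the protection of randomisation, and it is right for MACE counted from randomisation. The article also makes both situations unlikely: dosing starts at Visit 1, and a numbered box is released by a central call. The shifts are smaller than one patient's weight in most scenarios (one event in 40 is 2.5 points). All of this stands. It limits the size and shapes the fix, but it does not make a by-assignment set the best main analysis of adverse events.

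Three stronger readings are tempting and not supported.
- A reader might infer that the rule always hides harm. Only misallocated product always shrinks the expected contrast. Never-dosed patients mainly on placebo can widen it (10 to 11 points above), and balanced never-dosing with no events leaves the risk ratio unchanged. Blinding makes balance the reasonable expectation, but the article gives no data on it.
- A reader might infer that never-dosed patients are counted as exposed and event-free. Intention-to-treat counts whatever events they report, and patients with coronary disease have background events. The zero-event rows are therefore the largest dilution, not the expected one.
- Section 5.8 also says "As dealing the missing values, last-observation-carried-forward method will be applied" without exempting safety data. A reader might infer that baseline laboratory values of an undosed patient will be carried forward as no change. The article does not say whether the rule is meant for safety tests.

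**Conclusion.** The point holds as a minor one. Section 5.8 fixes a by-assignment safety analysis, and nothing else in the article offsets it. Misallocated product pulls the difference towards zero. Never-dosed patients with few events lower their own arm's rate, and they shrink the risk difference when balanced or mainly on THJG.

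For the balanced scenarios worked here (1 to 4 never dosed and 0 to 2 wrong boxes per arm of 40), the difference keeps 81% to 97.5% of its size. A 20% rate falls by 0.5 to 2 points for 1 to 4 event-free undosed patients. All counts and event rates are assumptions. If every patient takes at least one dose of the assigned product, the two analyses coincide.

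**What to change.** Split the sentence in section 5.8.
- Keep intention-to-treat for efficacy and for MACE counted from randomisation.
- For adverse events and laboratory safety, make the main analysis all patients who took at least one dose, grouped by the product actually received.
- Show the by-randomised-group result alongside.
- List every patient whose safety group differs from the randomised group.

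Add the dispensed box number to the CRF, to be checked against the random list after unblinding. Section 4.3 already requires name, dosage and duration of any intervention to be recorded, which should identify patients who took nothing, but no section says that the box number is captured. This check finds dispensing errors only: a box mislabelled at the factory would carry the right number and pass.

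The cost is a short rewording of section 5.8, one CRF field and one extra analysis flag. Sample size, visits and the efficacy analysis are unaffected.

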### TCM intervention

4.1

In THJG group, patients will be instructed to dissolve THJG (18.3 g) in 200 mL hot water and take the solution orally twice a day for 4 weeks, while patients in the placebo group will take THJG placebo in the same way.

The THJG will be manufactured, packaged, and labeled by PuraPharm Corporation in Nanning (website: https://www.purapharm.com/zh-hans/). THJG is made from the following ingredients: *Semen persicae* (Taoren, 10 g), *F carthami* (Honghua 10 g), *R corydalis* (Yanhusuo, 10 g), *R chuanxiong* (Chuanxiong, 10 g), *R paeoniae rubra* (Chishao, 10 g), *R salviae miltiorrhizae* (Danshen, 15 g), *R angelicae sinensis* (Danggui, 12 g), *R rehmanniae* (Shengdi, 10 g), *P citri reticulatae viride* (Qingpi, 10 g), *R cyperi* (Xiangfu, 10 g), and *Olibanum* (Ruxiang, 3 g).

*Processing:* Extraction: all the herbs mentioned earlier are put into a water-filled container. After a 30-minute immersion, the mixture is boiled at 100°C for 1 hour. Filter out herbal sediments, and gather herbal filtrate; Concentration: concentrate the herbal filtrate; Granule: mix the concentration with dextrin. The mixture is spray dried to generate dry mash. Then mix the dry mash with magnesium stearate into powders, shattered and screened with a mesh size of 80. Finally, the THJGs are packed in individual bags (18.3 g per bag).

For the control group, THJG placebo contains 90% bitterant, edible lactose, starch, and pigment (such as lemon yellow, caramel pigment, and sunset yellow), are also made from 10% THJG to achieve the similar color, smell, taste, and texture as THJG.

At baseline (Visit 1), patients begin to receive THJG or THJG placebo and laboratory tests. At weeks 2 and 4, patients will visit again (Visits 2 and 3) and perform laboratory tests. Medicine intervention will be finished at week 4. Then at week 8, the follow-up visit (Visit 4) will be taken through a phone call. Every patient should visit and do laboratory tests within 3 days after the original time point.

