#### Integral TCM syndrome score (from baseline to week 4)

5.1.1

Integral TCM syndrome score is a widely used system to evaluate the efficacy of Chinese herb treating SCAD patients, which are stagnant Qi and blood type in China.^[11]^ This assessment form is constitutive of 2 parts: symptom part and sign part. In detail, there are total 8 appraisable items, angina, chest distress, palpitation, vexation, insomnia, lassitude, dizziness, and color of lips and snails, respectively. Each item consists of 4 levels and regarding scores. Wholly, the minimum score is 0 and the maximum score is 33. The higher scores of participants mean a severer condition. The scores and details of TCM syndrome are given in Tables 2 and 3.

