#### Integral TCM syndrome score (from baseline to weeks 2 and 8)

5.2.1

Integral TCM syndrome score from baseline to weeks 2 and 8 will be calculated as one of the secondary outcomes.

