### Data collection and monitoring

5.5

In this 8-weeks’ trial, all participants will be treated with THJG or THJG placebo for 4 weeks and followed-up for another 4 weeks. Five rounds (the baseline, week 2, week 4, and week 8) of disease evaluations and safety evaluations, and 2 rounds (the baseline, and week 4) blood examinations will be recorded in CRFs at each visit point, then entered in Epidata software (Version 3.1) by 2 statisticians independently every month. Difference will be solved by discussion and a 3rd party. All the trained data processors come from the CRC to keep the quality of data collection.

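### Carrying the last observation forward, fixed as the only rule for missing values, can bias the week-4 primary comparison and fills missed off-treatment week-8 visits with on-treatment scores

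*Protocol article*

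**What the plan says.** The protocol article, section 5.8 (Statistical analysis), gives one rule for missing data: "As dealing the missing values, last-observation-carried-forward method will be applied". The same paragraph says "Intention-to-treat approach for effectiveness and safety analysis will be used" and names a Student t test, or a nonparametric test where normality fails. Nothing limits the rule to certain outcomes, visits or reasons for missingness.

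The visit structure is as follows:

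- The primary outcome is the TCM syndrome score from baseline to week 4 (section 5.1.1). The only earlier scores are those at baseline and week 2.
- On treatment, section 4.1 says "Medicine intervention will be finished at week 4" and "Then at week 8, the follow-up visit (Visit 4) will be taken through a phone call". Section 5.5 confirms that patients are "treated with THJG or THJG placebo for 4 weeks and followed-up for another 4 weeks".
- For the secondary outcomes, section 5.2.1 says "Integral TCM syndrome score from baseline to weeks 2 and 8 will be calculated as one of the secondary outcomes". The Seattle Angina Questionnaire (SAQ), Athens Insomnia Scale (AIS) and SF-36 are assessed at weeks 2, 4 and 8, and major adverse cardiovascular events (MACE) are counted to week 8.
- Section 5.5 records blood examinations at baseline and week 4 only, although section 4.1 also mentions laboratory tests at week 2.
- Patients may withdraw at any time (section 5.3). No dropout rate is given.

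**The concern.** The trial looks for a change in symptoms over four weeks of treatment. For a patient who leaves early, a carried baseline score imputes no change at all, and a carried week-2 score imputes a half-course response. Either value then enters the t test with the same weight as a measurement, so the standard error does not reflect that it was imputed. If dropout or its timing differs between arms, the rule can create or hide a difference even when the data are missing at random.

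At week 8 the mechanism is different. A missed phone visit is replaced by a score taken on treatment, which assumes that nothing changed after treatment stopped.

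Two further effects follow from the rule having no limits. On the two-round blood schedule, a missing week-4 marker becomes zero change. Applied to MACE, the rule would count a patient lost to follow-up as event-free.

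**Working it through.** The article gives no dropout rate and no time course for the score, so there is no figure of its own to reproduce on this point.

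**From section 5.7:** difference 4, SD 7.7, 40 per arm. The standard error of the difference is 7.7 × √(2/40) = 1.72.

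**Assumed:** dropout rates, mean changes, and half of the week-4 change reached by week 2. Whether baseline counts as an observation to carry is not stated, so both cases are shown. Lower scores are better, so improvement is negative.

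**Formula for each arm:** expected mean change = (1 − d) × week-4 change + d × carried change, where d is the dropout proportion.

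*Week 4, true difference 4, equal dropout*

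- Week 2 carried: 4 × (1 − d/2) = 3.8 at 10% and 3.6 at 20%.
- Baseline carried: 4 × (1 − d) = 3.6 at 10% and 3.2 at 20%.

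*Week 4, changes −8 (THJG) and −4 (placebo), dropout 20% and 10%*

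- Week 2 carried: THJG −8 × 0.8 − 4 × 0.2 = −7.2; placebo −4 × 0.9 − 2 × 0.1 = −3.8; difference 3.4.
- Baseline carried: −6.4 and −3.6; difference 2.8.

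These are 15% and 30% below the true 4.

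*Same changes, dropout 5% (THJG) and 20% (placebo)*

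- Week 2 carried: −7.8 and −3.6; difference 4.2.
- Baseline carried: −7.6 and −3.2; difference 4.4.

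The error can therefore go either way.

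*Week 4, no true effect, both arms −6, dropout 20% (THJG) and 10% (placebo)*

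- Week 2 carried: −5.4 and −5.7; spurious 0.3 in favour of placebo.
- Baseline carried: −4.8 and −5.4; spurious 0.6.

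With bias b, the two-sided type I error is about 1 − Φ(1.96 − b/1.72) + Φ(−1.96 − b/1.72). That is 5.3% for b = 0.3 and 6.4% for b = 0.6. With equal dropout at the same times and no true effect, b = 0. A more extreme case (5% versus 20% dropout, both arms improving by 8, baseline carried) gives b = 7.6 − 6.4 = 1.2 and about 10.7%.

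*Week 8, week-4 difference 4, proportion q missing in each arm and filled from week 4*

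Expected difference = (1 − q) × true week-8 difference + q × 4.

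| True week-8 difference | q = 10% | q = 20% | q = 30% |
|---|---|---|---|
| 0 (effect gone) | 0.4 | 0.8 | 1.2 |
| 2 (half remains) | 2.2 | 2.4 | 2.6 |
| 4 (all remains) | 4.0 | 4.0 | 4.0 |

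**The case against.** The strongest defence is that the harm may be small. Treatment lasts four weeks with a visit halfway, so little time is being bridged. With equal dropout of 10% to 20% and week 2 carried, a true 4 points falls only to 3.8 to 3.6, which is towards no difference. The spurious 0.3 to 0.6 points is 0.17 to 0.35 of a standard error. The larger figures need baseline to be carried, unequal dropout, or both. All of this stands, and it limits the size of the point. It does not rescue the rule: the method is not reliably conservative, as the 4.2 to 4.4 and week-8 results show, and dropout cannot be known when the rule is set.

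A reader might infer that the primary comparison is biased as planned. The article does not support that. The bias is zero if nothing is missing, and also with equal dropout and no true effect.

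A reader might also infer that the week-8 rule assumes the answer to a main question of the trial. No section states persistence after treatment as an objective. Week 8 is a secondary time point and cannot affect the week-4 primary result.

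Nor does the lack of a named sensitivity analysis count against the article, since that may stand in an analysis plan not shown. The carrying-forward rule is different, because it is stated outright. If an analysis plan says otherwise, the two need to be reconciled.

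**Conclusion.** The point holds as a risk built into a stated rule, and the change is worth making. Carrying the last observation forward can bias the week-4 comparison in either direction, it treats imputed scores as measured, and at week 8 it mixes on-treatment scores into an off-treatment comparison. In the main scenarios, a true 4 points is reported as anything from 3.8 down to 2.8. A null effect shows 0.3 to 0.6 points against a standard error of about 1.7, and a vanished week-8 effect shows 0.4 to 1.2 points. Every one of these figures rests on assumed dropout, and the week-4 figures also on an assumed course of the score. The principle is firm, but the actual effect on this trial cannot be known from the article.

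**What to change.** Replace the rule in section 5.8, and in any analysis plan, as follows:

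- **TCM score, SAQ, AIS and SF-36:** a mixed model for repeated measures on all observed values, with baseline as covariate; treatment, visit and treatment-by-visit as fixed effects; and an unstructured covariance. For the TCM score, the week-4 contrast is primary and week 8 is secondary. The model is valid when data are missing at random, which carrying forward in general is not.
- **Blood markers with one post-baseline value:** a baseline-adjusted analysis of the observed values. The wording of sections 4.1 and 5.5 on week-2 tests should be aligned, so that it is clear which markers these are.
- **MACE:** do not carry observations forward; state how patients lost before week 8 are counted.
- **Optional:** a sensitivity analysis that imputes THJG dropouts from the control arm. It should note that the placebo itself contains 10% THJG (section 4.1).

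The cost is a change of wording and a little more analysis work. The mixed-model procedure is available in the named software, and the scores are already collected at every visit needed. The control-based imputation, if used, takes some extra programming. The main downside is that the stated t test or nonparametric test is no longer the primary test for these scores, so the change should be made before unblinding.

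### The primary score is to be compared without baseline adjustment, by a test chosen after a normality check; a prespecified ANCOVA would be more precise and would fix the effect measure in advance

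*Protocol article*

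**What the plan says.** Protocol article, section 5.1.1 defines the primary outcome as "Integral TCM syndrome score (from baseline to week 4"), so every patient should have a baseline value. It describes a sum score for which "the minimum score is 0 and the maximum score is 33".

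Section 5.8 has no separate rule for the primary outcome. Its general rule is "Continuous variables, which are kept in the normal distribution, will be analyzed by Student" *t* test; "or else, nonparametric tests will be adopted". The section names no covariate, no criterion for normality and no particular nonparametric test. It does not say whether the quantity compared is the week-4 score or the change from baseline.

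Section 5.7 sizes the trial on a difference in means: ("the difference of integral TCM syndrome score of THJG and control group) = 4", with ("standard deviation of 2 groups) = 7.7" and 40 patients per group, "to achieve a 90% power and a 2-sided 5% significance level". It does not say whether 7.7 is the SD of the week-4 score or of the change.

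**The concern.** There are two separate weaknesses.

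**Precision.** A two-sample t test or a simple nonparametric test makes no regression adjustment for baseline. If week-4 scores are compared, baseline is not used. If changes are compared, baseline is subtracted with a fixed coefficient of 1, which over-corrects whenever the regression slope of week-4 on baseline is below 1. In both cases part of a chance baseline difference between two groups of 40 stays in the estimate, and the standard error is larger than it needs to be.

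**An unfixed effect measure.** The trial is sized on a 4-point difference in means. If the observed scores are judged non-normal, the primary comparison becomes nonparametric, and that mean difference is no longer what is tested. A bounded sum of eight four-level items may well be non-normal, so the switch is a realistic prospect.

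The stake is precision in a small trial, and a primary result whose form is known only after the outcome data have been seen.

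**Working it through.** **Inputs.** From section 5.7: difference 4, SD 7.7, 40 per group, two-sided 5%, target power 90%. Assumed: baseline-to-week-4 correlation r of 0.3, 0.5 or 0.7 (the documents give none), and equal SDs at baseline and week 4.

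**1. The plan's own figure.** Number per group = 2 × [7.7 × (1.96 + 1.282) / 4]² = 2 × 6.241² = 77.9, so 78 per group (156 in total). The stated 80 in total is not reproduced. At 40 per group the standard error is 7.7 × √(2/40) = 1.722 and the noncentrality is 4/1.722 = 2.323. With 78 degrees of freedom, power by the noncentral t is 63%. This is the power of a t test on whichever quantity has SD 7.7.

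**2. Residual SDs.**
- 7.7 is the week-4 SD: ANCOVA 7.7 × √(1 − r²); change-score t test 7.7 × √(2(1 − r)).
- 7.7 is the SD of change: the week-4 SD is 7.7/√(2(1 − r)), so ANCOVA has 7.7 × √((1 + r)/2).

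**3. Power at 40 per group, difference 4** (noncentral t; 77 df for ANCOVA, 78 for t tests).

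| r | Week-4 SD = 7.7: t test on week-4 score | t test on change | ANCOVA | Change SD = 7.7: t test on change | ANCOVA |
|---|---|---|---|---|---|
| 0.3 | 63% | 49% (SD 9.11) | 67% (SD 7.35) | 63% | 81% (SD 6.21) |
| 0.5 | 63% | 63% (SD 7.70) | 75% (SD 6.67) | 63% | 75% (SD 6.67) |
| 0.7 | 63% | 84% (SD 5.96) | 89% (SD 5.50) | 63% | 70% (SD 7.10) |

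ANCOVA is ahead in every row. The gain runs from 4 points (67% against 63%) to 26 points (89% against 63%), depending on r, on which quantity the SD describes and on which t test is meant.

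**4. When would 40 per group give 90%?** If 7.7 is the week-4 SD, r must be about 0.70 or higher. If 7.7 is the SD of change, r must be close to 0.

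**5. Chance imbalance.** Take a baseline SD of 7.7 (assumed). One standard error of the baseline difference is then 1.72 points. Given a baseline difference D, the week-4 comparison is shifted by r × D and the change comparison by (r − 1) × D. At r = 0.5 and D = 1.72, each shift is 0.86 points in size, and 0.86/4 = 22% of the target difference. ANCOVA removes this expected shift.

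**6. The normality condition.** The two-stage rule was simulated under no treatment effect, with 10,000 trials of 40 per arm. It used a Shapiro-Wilk test at 5% in each arm, then a t test or a Mann-Whitney test. Both tests are assumptions, because the plan names neither.

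| Score distribution | Switched to Mann-Whitney | Type I error |
|---|---|---|
| Normal | 10% | 5.1% |
| Skewed, rounded, limited to 0–33 | 99% | 4.4% |

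The error rate stays near 5%. What varies is which comparison is made.

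**The case against.** The strongest case against is that the plan is valid as it stands. In a randomised trial an unadjusted t test is a legitimate comparison. The sentence in section 5.8 is a general rule in a condensed article, and the covariates, the normality criterion and the name of the nonparametric test could be in a document not shown. That stands as far as missing detail goes, and no point is made of it here. But the article does state a rule that makes the test depend on the observed distribution, and it sizes the trial on a difference in means. That rule can be judged on its own terms.

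Four stronger readings are tempting and should not be drawn.

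- *A reader might infer that the plan ignores baseline altogether.* If change is analysed, baseline is subtracted and only the regression-to-the-mean part of an imbalance remains. The text leaves open which quantity is compared.
- *A reader might take the gain as a fixed amount, such as 63% to 89%.* That sets ANCOVA against a t test on week-4 scores. Under the same SD and correlation, a change-score t test already has 84%.
- *A reader might infer that the normality condition inflates false positives.* The simulation shows no material inflation.
- *A reader might infer that adjustment can never lose power.* That was checked for r from 0.3 to 0.7 with baseline as the only covariate. With several covariates of little prognostic value and r of 0.2 or below, power could be about 61–62% against 63%. That loss is trivial, but it rules out a universal claim.

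The shortfall against 90% power is a separate defect of section 5.7. It makes lost precision more costly, but this point does not depend on it.

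**Conclusion.** The point holds in limited form. The stated primary analysis is valid, but it is less efficient than ANCOVA over the range examined, and it does not settle in advance whether a mean difference or a nonparametric comparison will be the primary result. At 40 per arm, ANCOVA would have roughly 67–89% power if 7.7 is the week-4 SD, against 63% for a t test on week-4 scores or 49–84% for one on change. If 7.7 is the SD of change, it would have 81–70% against 63%.

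These figures rest on assumed correlations of 0.3 to 0.7, equal variances at the two visits and complete data. They leave out the small loss from chance imbalance in the covariates. The documents cannot say where in the range the trial lies. Adjustment would not by itself deliver the stated 90% unless the correlation happens to be favourable. The change is worth making, but the present plan is not invalid without it.

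**What to change.** In section 5.8, and in the statistical analysis plan, name one primary analysis: ANCOVA of the week-4 TCM syndrome score on treatment and baseline score. Report the adjusted mean difference with its 95% confidence interval, whatever any normality test shows. Keep a nonparametric comparison only as a sensitivity analysis, with the test named. Say in section 5.7 which quantity the SD of 7.7 describes.

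Centre may be added. With the four sites listed in section 2.1, it takes three further degrees of freedom (77 to 74), which lowers power by less than 0.1 percentage point in the scenarios above.

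The cost is wording only. Baseline score and centre are already recorded, and no visit, measurement or patient is added.
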